#### Moderators/Mediators

##### Coping Self Efficacy

Self-efficacy will be measured using a scale previously developed by Lepore and colleagues for men with prostate cancer [25]. This scale measures how certain men are that they will be able to control side effects, manage stress, understand their illness and communicate effectively with physicians and family.

##### Social Support

Social support will be assessed using the MOS Social Support Survey [26].

##### Social Constraints

The Social Constraints Scale (SCS) [27] will assess the extent that men perceive they cannot talk freely about cancer-related concerns and feelings with others. The SCS has good reliability and predicts adjustment to prostate cancer [28].

##### Group Cohesion

Cohesion within the peer support groups will be measured with the Perceived Cohesion Scale [29].

##### Therapeutic Alliance

The quality of the bond between the peers and men in the tele-based group peer sessions will be assessed by the Working Alliance Inventory [30].

#### Primary Outcome Variables

##### Unmet Supportive Care Needs

The Supportive Care Needs Survey Short Form 34 (SCNS-SF34) will assess patients' need for help over the last month across 5 domains: psychological, health systems and information, patient care and support, physical and daily living, and sexuality needs [31]. It has well demonstrated reliability and validity in cancer populations. An 8-item prostate cancer-specific module will be added to the standard scale [32].

##### Physical Activity

All men will complete the Godin Leisure-Time Exercise Questionnaire [33]. This questionnaire assesses the average frequency of mild, moderate and strenuous exercise during free time in a typical week. Motivational readiness for physical activity will be assessed with a four item scale that asks about current levels of physical activity and intention to become more physically active [34]. In addition, men in the intervention arm only will complete simple activity diaries assessing mode, duration and intensity of physical activity entering data from the heart rate watches provided for a seven day period at the baseline assessment before the intervention commences.

#### Secondary Outcome Variables

##### Domain Specific QoL

The International Prostate Symptom Score [35] and symptom and bother subscales of the Expanded UCLA Prostate Cancer Index [36,37] will assess disease-specific QoL.

##### Health-related QoL

The AQoL-8D examines health-related QoL over eight dimensions (e.g. independent living, mental health, relationships) and allows a simple global utility score to be calculated [38] which is essential for the derivation of Quality-adjusted-life-years (QALYs). QALYs are a useful generic outcome in economic evaluation allowing inferences regarding value-for-money to be made.

##### Psychological Distress

Brief Symptom Inventory-18 [39] will provide a global measure of current psychological distress with subscales of anxiety, depression and somatisation. Somatisation and anxiety have been found to be related to physical activity levels in colorectal cancer survivors [40].

##### Distress Screening

The single item Distress Thermometer will assess global psychological distress [41,42].

##### Positive Adjustment

Positive adjustment will be measured with the Posttraumatic Growth Inventory assessing perceived positive outcomes resulting from a diagnosis of cancer [43]. Domains include new possibilities, appreciation of life, personal strength, relating to others, and spiritual/religious change. This scale has been previously validated with cancer patients.

##### Body mass index (BMI) and waist circumference

Participants will be asked to measure their body weight and height. BMI will be calculated as weight/(height × height). Waist circumference will be measured using a cloth tape measure provided to the men with their intervention materials. Both BMI and waist circumference have been validated as indicators of overweight or obesity and correlate with cardiovascular disease and metabolic syndrome risk [44]. Self-measured height, weight and waist circumference is accurate and valid if appropriate instruction is provided [45].

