### Intervention

Usual care will consist of the man's standard medical management and a package containing existing evidence-based patient education materials. The multimodal supportive care intervention "Living with Prostate Cancer" will include self-management and tele-based group peer support. All men in the multimodal intervention condition will receive a printed feedback sheet with baseline assessments of unmet need, their distress thermometer score, body mass index, waist circumference and physical activity levels. This will assist them to identify potential target areas for improvement; evaluate prime concerns; and set self-management goals. As well, a password protected website will be developed utilising Web 2.0 technology to guide men through program materials and other relevant existing web-based resources in an interactive online environment. This will allow each man to access other topic areas should his needs change; locate misplaced resources; access other helpful resources; and interact with other men in the study.

The exercise module of the intervention will focus on low cost strategies that are easily implemented in any geographic area. Participants will be encouraged to meet the physical activity targets recommended for cancer survivors [18-20]. Each participant will be provided with an elastic exercise device (Gymstick, Finland) and a watch with heart rate monitor (Polar, Finland) so that all men have the basic equipment to pursue an effective exercise program even in rural or remote settings with no additional facilities.

The tele-based group peer support will be conducted through teleconference and will be co-facilitated by a nurse counsellor and experienced trained peer. A peer is a man who has been previously diagnosed with prostate cancer and who is physically and emotionally well enough to provide support to others. The focus of the peer support groups will be on sharing experiences to facilitate peer learning, coping self-efficacy, emotional/social support and processing of experiences. The groups will have up to eight members and will be formed as men are recruited. Groups will run for six months with monthly teleconferenced meetings.

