### Study Integrity

Ethical approval has been obtained from the Griffith University Human Research Ethics Committee (Approval: PSY/F6/10/HREC). The study design will be guided by the CONSORT criteria [24]. Randomisation to study condition will occur following the completion of baseline assessment. Assessments will be by telephone and self-report written questionnaires and project staff tracking assessments will be blinded to condition where possible. Randomisation will occur in blocks of 16, with each condition randomly generated 8 times within each block to ensure an unpredictable allocation sequence with equal numbers of men in each condition at the completion of each block; and sufficient men to form a tele-based group (of 6-8) in the multimodal supportive care condition. This sequence will be undertaken by the project manager and concealed from investigators. The group sessions will be audiotaped with 25% reviewed to ensure adherence to a peer support approach. Analyses will be conducted on the basis of intention to treat.

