### Measures

A series of previously validated and reliable self-report measures will be administered to men at four time points: baseline/recruitment (when men are approximately 3-6 months post-diagnosis) and at 3, 6, and 12 months after recruitment and intervention commencement. Baseline assessments will be conducted by telephone to facilitate completion of assessments prior to randomisation. Follow-up assessments will be conducted through written questionnaires that will be mailed to participants. Social constraints, social support, self-efficacy, group cohesion and therapeutic alliance will be included as potential moderators/mediators of intervention effect. Primary outcomes are unmet supportive care needs and physical activity levels. Secondary outcomes are domain-specific and health-related QoL; psychological distress; benefit finding; body mass index and waist circumference (the following list describes the measures in detail). Disease variables (e.g. cancer Gleason score, stage) will be assessed through medical and cancer registry records.

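### The stated supply route for the waist tape cannot serve the pre-randomisation baseline and, on the plain reading, leaves usual-care men without the supplied instrument, so this secondary outcome is open to differential measurement

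*Protocol article*

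**What the plan says.** The Measures section names waist circumference among the secondary outcomes ("benefit finding; body mass index and waist circumference (the following list describes the measures in detail"), with assessments at baseline and at 3, 6 and 12 months.

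The section on body mass index and waist circumference states how the instrument reaches the men: "Waist circumference will be measured using a cloth tape measure provided to the men with their intervention materials". It then rests the validity of self-measurement on a condition: "Self-measured height, weight and waist circumference is accurate and valid if appropriate instruction is provided".

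On timing, Study Integrity says "Randomisation to study condition will occur following the completion of baseline assessment". Measures agrees for baseline ("Baseline assessments will be conducted by telephone to facilitate completion of assessments prior to randomisation") and says of later assessments: "Follow-up assessments will be conducted through written questionnaires that will be mailed to participants".

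The Intervention section says that men in the multimodal arm receive "a printed feedback sheet with baseline assessments of unmet need, their distress thermometer score, body mass index, waist circumference and physical activity levels". Of the other arm it says: "Usual care will consist of the man's standard medical management and a package containing existing evidence-based patient education materials".

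**The concern.** The tape sentence ties the instrument to materials that follow allocation, while the outcome is measured in everyone and first measured before allocation. Two consequences follow.

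- **Baseline.** The supplied tape is not available for the baseline value in either arm, although the feedback sheet has to report that value and is meant to guide goal-setting.
- **Follow-up.** If the tape goes to one arm, intervention men measure with the supplied tape and usual-care men with whatever they have. That is a difference in method introduced after randomisation and aligned with treatment. Neither randomisation nor intention-to-treat analysis removes it. Adjusting for baseline does not remove it either, because the method changes between baseline and follow-up in one arm and not in the other.

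A systematic offset between the two ways of measuring would then appear as a treatment effect or hide one. Men without a tape might also leave the item blank more often, although the document gives no figure on this.

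**Working it through.** **Step 1: the sequence.**

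| Event | Source in the protocol article | Supplied tape in hand? |
|---|---|---|
| Baseline by telephone | Measures | No, in neither arm |
| Randomisation, after baseline | Study Integrity | – |
| Intervention materials, including the tape | Intervention; BMI and waist section | Intervention arm from here |
| Usual-care education package | Intervention | No tape mentioned |
| Mailed questionnaires at 3, 6 and 12 months | Measures | Intervention yes; usual care no, on the plain reading |
| Feedback sheet with baseline waist | Intervention | Needs a value taken without the supplied tape |

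The baseline conflict is firm. It holds even if the intervention materials are read generously to include the usual-care package, because a package specific to the condition also has to wait for allocation. The follow-up difference rests on the plain reading of which men receive those materials.

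**Step 2: the sample size used as context.** The Participants section gives 250 completers per arm and 15% attrition: 500 / (1 − 0.15) = 588.2, rounded up to 589. This agrees with the stated figure of about 590, or 295 per arm. Nothing in the point depends on it.

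**Step 3: how large an offset would matter.** The document gives neither a waist SD nor a difference between methods. Both are assumptions here: SD 10 to 12 cm, offset 1 to 3 cm.

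- Difference detectable with 80% power, two-sided 5%: (1.96 + 0.84) × √(2/250) = 2.80 × 0.0894 = 0.25 SD, which is 2.5 cm at SD 10 and 3.0 cm at SD 12.
- Offset in SD units: smallest 1/12 = 0.08, largest 3/10 = 0.30.

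**Step 4: false-positive rate with no true effect.** For a simple comparison at one follow-up visit, SE = SD × √(2/250), which is 0.894 cm at SD 10 and 1.073 cm at SD 12. The rejection rate is Φ(offset/SE − 1.96) + Φ(−offset/SE − 1.96).

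| Assumed offset | SD 10 cm | SD 12 cm |
|---|---|---|
| 0 cm | 5% | 5% |
| 1 cm | 20% | 15% |
| 2 cm | 61% | 46% |
| 3 cm | 92% | 80% |

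These rates show sensitivity only. They do not estimate what will happen in this trial.

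**The case against.** A reader might infer that the protocol withholds the tape from controls and that the waist comparison is therefore biased. The documents do not support so strong a statement, for these reasons.

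- **No sentence says that only one arm gets a tape.** The BMI and waist section speaks of participants and of the men in general. Where a measure is confined to one arm, the Physical Activity section says so outright for the activity diaries. The wording could loosely mean each man's study pack. This stands: the arm difference is an inference, though it is the ordinary reading, since the Intervention section lists no tape for usual care.
- **The authors need a baseline waist value, so they may have intended a mailing to all men before randomisation.** This is plausible, and Figure 1 is not available to settle it. It would make the sentence wrong as written rather than harmless, because staff following it would send the tape after allocation.
- **The baseline gap does not itself bias the comparison.** Correct. Before randomisation all men are in the same position. The risk of bias lies at follow-up.
- **A different tape is not a biased tape.** Correct. Random error from improvised measuring costs precision, and only a systematic offset moves the mean difference. The document shows no offset. It also does not say that instruction is withheld from either arm; the mailed questionnaires could carry it.
- **The magnitude is assumed.** Correct. The offset reaches the detectable difference only at the top of the range (2.5 cm at SD 10, 3 cm at SD 12). At 1 cm it is 0.08 to 0.10 SD.
- **Mailing logistics belong in a fuller protocol.** True of detail left out. Here a route is stated, and it does not fit the article's own sequence.

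**Conclusion.** The point holds in limited form. It is firm that the tape, sent as the article states, cannot be in use for the baseline waist value that the feedback sheet requires. On the plain reading, which is an inference, usual-care men are not supplied with a tape. The comparison of this outcome is then open to differential measurement, and possibly differential missingness, at follow-up, with a change of method from baseline in the intervention arm only.

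The size and direction of any offset are unknown. Under the stated assumptions it could lie anywhere from about a third of the detectable difference (0.08 against 0.25 SD) to slightly above it (0.30 SD). If the methods agree on average, there is no bias.

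Severity is minor to moderate. One secondary outcome is affected, none of the four hypotheses names it, and neither primary outcome nor the sample size depends on it. The reason to settle it before enrolment is that a baseline value taken by another method cannot be recovered later.

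**What to change.** Send the same cloth tape and the same written measuring instructions to every man before the baseline call, and have both arms use them at all four assessments. Reword the tape sentence so that it no longer links the tape to the intervention materials and states when, and to whom, tape and instructions go. If all men already receive the tape before baseline, correcting that sentence is enough.

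The cost is about 295 more tapes (590 / 2), an earlier mailing, and the small drawback that usual-care men also receive a tape.

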##### Economic Evaluation Variables

Participants will be given a cancer care diary to fill-out with respect to all appointments and treatments they receive throughout the follow-up period. The diary includes utilisation and out-of-pocket costs for services such as hospitalisation, medication, other allied health consultations and use of alternative therapies. Items such as medications will be cross-checked against medical records to ensure all medications are captured. The diary also measures days out-of-role (including paid and unpaid work) as well as travel costs so that a broader economic societal perspective may be undertaken. These questionnaires have been found to be reliable in estimating resource use. In addition, research team and provider records will be used to determine the costs of the multimodal supportive care intervention. Measured resource use will be valued using existing unit costs from sources such as the Medical Benefit Schedule fee rates for medical attendances; AN-DRG costs of hospitalisation; and Australian Bureau of Statistics estimates of Australian earnings [46].

##### Group communication analysis

The group peer support telephone sessions will be audio-taped and transcribed to allow in-depth analysis of men's interactions during these group sessions.

### Statistical Analyses

This study is a multivariate, two-condition randomised controlled trial with repeated measures across time and continuous and dichotomous outcome variables. The analysis of longitudinal differences in outcome will use two complementary statistical approaches: multilevel (mixed) modelling (MLM) and growth mixture modelling (GMM) as applied to randomised preventative interventions by Muthén [47]. These procedures allow the testing of typical group level predictions such as Hypothesis 1 that men in the intervention condition will have better outcomes than the usual care group. However, by incorporating the hierarchical structure of assessment points nested within individual men they further permit the true assessment of individual change in unmet needs and of the individual predictors of such change (Hypotheses 2 and 3). Consequently (and unlike traditional approaches), such models deal with the heterogeneity of responses, such as that expected in the outcomes of the proposed study, by including such variation as an explicit model term. MLM and GMM have the advantages of allowing use of all available data points, which maximizes power to detect effects and reduces bias owing to missing data in longitudinal studies.

The economic evaluation will be a cost-consequences analysis conducted from both the broad societal perspective and the narrower perspective of the health care sector [48]. The economic evaluation will compare any incremental costs of the intervention (costs accrued in the intervention arm compared to costs accrued in the control arm) to the full list of incremental outcomes. The AQoL-8D will allow utility values to be determined (which are used in calculating Quality-Adjusted Life Years (QALYs)) for a cost-utility analysis, which is a more optimal design since QALYs allow comparisons across conditions. The evaluation will include only the costs of intervention delivery (excluding development or research costs), to estimate the resource use required if the multimodal supportive care intervention were rolled-out into practice. Uncertainty in the cost and outcome data and sensitivity of economic evaluation results to the methods of evaluation chosen will be tested through extensive sensitivity analyses. Depending on the results of the evaluation a longer life-time horizon may also be adopted [49].

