**Figure 1 F1:**
[figure not shown]
**Flowchart of recruitment, intervention and assessment**.

Inclusion criteria are that the men must: (1) have recently been diagnosed with localised prostate cancer (men will be three to six months post-diagnosis at recruitment); (2) be able to read and speak English; (3) have no previous history of head injury, dementia or psychiatric illness; (4) have no other concurrent cancer; (5) have phone access; and (6) have physician clearance to participate in the study. The diagnosing clinician will assist in determining eligibility as part of the consent process through the QCR.

Approximately 590 men will be recruited to the study (allowing 15% attrition from treatment; 250 men in each condition will complete final assessments). According to a Monte Carlo simulation run through Mplus, this sample size will provide between 80-85% power to detect standardised intervention effect sizes of .5 (moderate) for the dichotomous outcomes even with completion rates of 70% that are lower than the projected 85%. Power for the continuous outcomes is naturally higher for the same sample sizes, as evidenced by simulations by Jo and colleagues [23].

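### The longitudinal models are described with assessments nested within men only, although the intervention arm alone is treated in about 37 peer groups; if outcomes correlate within groups, the standard errors will be too small

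*Protocol article*

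**What the plan says.** The Statistical Analyses section chooses multilevel modelling and growth mixture modelling, says that they can test the between-arm comparison of Hypothesis 1, and explains their further value for Hypotheses 2 and 3 by "incorporating the hierarchical structure of assessment points nested within individual men". That is the only hierarchy named. The section mentions no peer-group level and no cluster adjustment.

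The Intervention section puts the men in the multimodal arm into teleconference groups that meet monthly for six months: "The groups will have up to eight members and will be formed as men are recruited". The Study Integrity section gives, as one reason for the block size of 16, that each block yields "sufficient men to form a tele-based group (of 6-8) in the multimodal supportive care condition". Usual care is standard management plus an education package, with no groups.

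The Background attributes the expected added benefit of peer support to mechanisms such as social support and learning from how peers cope. The Measures section lists group cohesion among the potential moderators and mediators.

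On power, the Participants section says that "this sample size will provide between 80-85% power to detect standardised intervention effect sizes of .5 (moderate) for the dichotomous outcomes", and adds that this holds even if only 70% complete, against a projected 85%. The source is given as a simulation: "According to a Monte Carlo simulation run through Mplus". For the other outcomes it says: "Power for the continuous outcomes is naturally higher for the same sample sizes". It reports no ICC and does not say whether the simulated data had groups.

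**The concern.** This is a partially nested design: clustered in one arm, unclustered in the other. Men who share a teleconference group for six months may end up more alike than men in different groups, and here that is part of the intended mechanism. A model whose only random structure is repeated assessments within men treats the men as independent of one another. With a positive ICC, the intervention-arm mean is then less precise than the model reports. Confidence intervals for the contrast are too narrow and the test rejects too often under the null. This reaches both primary outcomes through Hypothesis 1, and the other between-arm outcome comparisons. A power figure simulated without groups would also be too favourable.

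**Working it through.** **Inputs from the article.** About 590 men recruited, allocated 1:1, so 295 per arm; 15% attrition, 250 per arm completing; groups of up to eight (6-8), intervention arm only; power 80-85% for dichotomous outcomes at a standardised effect of 0.5 and 70% completion.

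**Assumptions.** ICC 0.02, 0.05 and 0.10 (none is given); two-sided alpha 0.05 (not given); normal approximation.

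**Reproducing the plan's figures.**
- Sample size: 500/0.85 = 588.2, so 589, against about 590. It reproduces.
- Power: 590 × 0.70 / 2 = about 206 men per arm. The control rate and the scale of the 0.5 effect are not given. Over control rates of 0.10 to 0.54, closed-form power is 28-71% if 0.5 is a log odds ratio and 61-99.6% if it is a standardised difference converted to the logit scale. Over control rates of 0.10 to 0.50, it is 71-98% if 0.5 is a probit shift. The 80-85% can be neither reproduced nor refuted, so it is taken as the starting point.

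**Number of groups.** 295/8 = 36.9, so about 37 full groups; with groups of seven or six, 295/7 = 42 or 295/6 = 49.

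**Analysed men per group (m).** A group of eight leaves 8 × 0.70 = 5.6 men at 70% completion and 8 × 0.85 = 6.8 at 85%. The type I error is shown for m = 5.6 and m = 7.

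**Formulas.**
- Design effect in the intervention arm: DE = 1 + (m − 1) × ICC
- Variance ratio of the contrast (equal arms, one clustered): VR = (1 + DE)/2
- Type I error if groups are ignored: 2 × [1 − Φ(1.96/√VR)]
- Power with clustering: Φ((1.96 + z_power)/√VR − 1.96), with z_power = 0.842 for 80% and 1.036 for 85%

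**Type I error of a nominal 5% test**

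| ICC | VR, m = 5.6 | Type I | VR, m = 7 | Type I |
|---|---|---|---|---|
| 0.02 | 1.046 | 5.5% | 1.06 | 5.7% |
| 0.05 | 1.115 | 6.3% | 1.15 | 6.8% |
| 0.10 | 1.23 | 7.7% | 1.30 | 8.6% |

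Worked example, m = 7, ICC 0.05: DE = 1 + 6 × 0.05 = 1.30; VR = 2.30/2 = 1.15; √VR = 1.072; 1.96/1.072 = 1.828; two-sided tail 6.8%. The true standard error is about 7% larger than the one reported.

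**Power, dichotomous outcomes, 70% completion (m = 5.6), if the 80-85% was simulated without groups**

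| ICC | Power |
|---|---|
| 0.01 | 79.1-84.2% |
| 0.02 | 78.2-83.4% |
| 0.05 | 75.6-81.0% |
| 0.10 | 71.4-77.1% |

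**Power at the projected 85% completion (m = 6.8).** Multiplying 1.96 + z_power by √(0.85/0.70) = 1.102 gives about 87-91% without clustering. With VR = 1.145 at ICC 0.05 it is 82-87%; with VR = 1.29 at ICC 0.10 it is 78-83%.

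**Continuous outcomes.** For a simple comparison of two means at d = 0.5 with 206 per arm and m = 8, power is 99.7% at ICC 0.05, 99.2% at 0.10 and 98.4% at 0.15.

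**The case against.** The strongest reply is that the quoted clause explains why these models can assess individual change. It is not a list of random effects, and nothing in it rules out a further level. The article condenses a fuller plan, and the exact random-effects structure is often settled there. This stands to the extent that the article does not state that a group term will be left out. It does not remove the point: the one hierarchy that is named is incomplete for this design, and an analyst following the text as written would fit no group effect.

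A reader might go further and infer that the standard errors are too small and the stated power is overstated. The document does not support either as fact. Both need a positive ICC, for which no figure is given, and the power claim also needs the Mplus simulation to have ignored groups, which is not reported. Nor should the 80-85%, which belongs to 70% completion, be combined with group sizes from 85% completion.

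The size can also be challenged. Much of the intervention is individual (feedback sheet, goals, website, exercise equipment), group contact is six monthly calls, and the 12-month assessment falls about six months after they end. The ICC could be small, and at 0.02 or less the effect is minor. The article does not say that membership is fixed or that each group keeps the same facilitators, so the point does not rest on that. The economic evaluation states no significance test, so false positives are not the issue there; only its uncertainty estimates are.

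**Conclusion.** The concern holds conditionally. The named model structure omits the peer groups, and for any positive ICC a model without them understates the standard error of the intervention contrast. For ICCs of 0.02 to 0.10 the true type I error is about 5.5% to 8.6%: slight at the low end, material at the high end. Generous power gives no protection here, because the error lies in the variance the test uses.

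The power consequence is weaker. It is limited to the dichotomous outcomes and to the case where the simulation had no groups; at 70% completion the loss is about 2 points at ICC 0.02 and about 8 points at 0.10. At the projected retention, power would probably stay above 80% at ICC 0.05.

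All of this rests on assumed ICCs, two-sided alpha 0.05, roughly equal group sizes and a normal approximation.

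**What to change.** - For Hypothesis 1 and the other between-arm outcome comparisons, prespecify a partially nested model: a random tele-group effect in the intervention arm only, each usual-care man as his own cluster, and small-sample degrees of freedom (Satterthwaite or Kenward-Roger). Equivalent cluster-robust errors are an alternative.
- Define group by the assigned group, so that men who never attend stay in the analysis and intention to treat is kept.
- Use cluster-robust errors by group in the growth mixture models, and resample whole groups in the intervention arm when expressing economic uncertainty.
- State the ICC and group size used in the power simulation, or show power over ICC 0.01 to 0.10.

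The cost is a sentence or two in the analysis section, a group identifier in the dataset, slightly wider intervals and a slightly less favourable power figure. No extra patients are needed. The choice should be fixed before outcome data are seen, because adding the term afterwards would be open to challenge.
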